### 2.14. Patient-Reported Outcome Measures

In further accordance with the consensus statement of Nano et al. [30], two generic and one diabetes-specific tool will be utilized at baseline, after the 12-week intervention period and at follow-up (translated in Arabic): The five-item WHO Well-Being Index (WHO-5), the Patient Health Questionnaire-9 (PHQ-9), and the Problem Areas in Diabetes (PAID) scale. In addition, as type-2 diabetes is associated with higher incidence of sleep disorders [38], sleep quality will be examined using the Pittsburgh Sleep Quality Index (PSQI) at baseline, after the 12-week intervention period and at follow-up. The WHO-5 and PHQ-9 have been shown to be valid and reliable screening tool for depression and as outcome measures in clinical trials [39,40]. Similarly, the PAID scale has been shown to be a valid, reliable, and sensitive research tool in patients with diabetes [41] and the PSQI has excellent test–retest reliability, specificity and validity in research and clinical settings [42]. Finally, changes in participants self-reported physical activity levels will be explored using the International Physical Activity Questionnaire short form (IPAQ-SF) [43].

### 2.15. Data Management

The collection and storage of data will adhere to the standard requirements of the UK Data Protection Act 2018. Data will be entered onto electronic spreadsheets, and then stored on a secure university server using Microsoft OneDrive(Microsoft, Washington, DC, USA). All data will be treated confidentially and anonymized for evaluation. Hard copies of data and documents will be kept in a locked and secure filing cabinet for the duration of the study. Following completion of the study, data will be transferred to the University of Central Lancashire Research Data Archive (CLOK), where it will be kept for 5-years. Hard copies will be disposed of confidentially and electronic data deleted after this period of time.

### 2.16. Statistical Analysis

All experimental data will be continuous and will therefore be presented as mean and 95% CIs. Statistical analysis of all baseline variables will be conducted to compare the two groups at baseline using linear mixed models, with group modelled as a fixed factor and random intercepts by participants. All analyses of the intervention-based data will be performed on an intention to treat basis and all randomized participants will be included in the final analysis as far as data collected will allow. Furthermore, in order to determine the effects of the intervention on all of the outcome measures, differences between the two groups will be examined using linear mixed models (at both 12-weeks and follow-up) with each group modelled as a fixed factor and random intercepts by participants adopted, adjusted for baseline values modelled as a continuous fixed covariate. For linear mixed models the mean difference (*b*), t-value and 95% confidence intervals of the difference will be presented. Finally, changes from baseline to follow-up in HbA1c will be used to create a binary variable i.e., improve/did not improve. Pearson chi-square tests of independence will be used to undertake bivariate cross-tabulation comparisons between the two trial groups, specifically to test differences in the number of participants who exhibited improvements in HbA1c. Chi-square probability values will be calculated using Monte Carlo simulation. All analyses will be conducted using SPSS v27 (IBM, SPSS, New York, NY, USA), and statistical significance accepted at the *p* ≤ 0.05 level.

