## Abstract

The Kingdom of Saudi Arabia is renowned for its high incidence of type-2 diabetes mellitus, with a prevalence rate of around 33%, which is expected to increase to 45.8% by 2030. Engagement in regular physical activity has been shown to significantly attenuate non-communicable diseases including type-2 diabetes. However, the overall rate of physical inactivity among Saudi Arabian adults is currently 80.5%, owing to time pressures, high-density traffic, poor air quality, lack of suitable exercise places/sports facilities, lack of social/friends support, gender, cultural barriers, low self-confidence, lack of time and environmental factors. Previous analyses have shown that home-based activity interventions can be effective. Therefore, given the aforementioned barriers to physical activity in Saudi Arabia; a home-based physical activity may be an ideal solution in type-2 diabetic patients. This manuscript describes the study protocol for a randomized control trial, examining the effects of a home-based physical activity intervention in Saudi Arabian adults with type-2 diabetes. The study will recruit 62 individuals with type-2 diabetes from the Jazan region of the Kingdom of Saudi Arabia, who will be individually randomized to either a physical activity or control group. This 24-week investigation will involve 12-weeks of physical activity in the physical activity group and feature three examination points i.e., baseline, 12-weeks and 24-weeks (follow-up). The primary study outcome is the between-group difference in blood HbA1c levels relative to controls. Secondary outcomes measures will be between-group differences in anthropometric, blood lipid, physical fitness, and patient-reported quality of life outcomes pertinent to type-2 diabetes. Statistical analysis will be conducted on an intention-to-treat basis. The trial has been granted ethical approval by Jazan University, Health Research Ethics Committee (REF: 2177) and formally registered as a trial (NCT04937296). We expect dissemination of the study findings from this investigation to be through publication in a leading peer-reviewed journal.

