## 2. Materials and Methods

### 2.1. Study Design and Setting

This investigation is described according to the updated guidelines for reporting parallel group randomized trials [27]. The trial will take place at the Jazan Diabetes and Endocrinology Center, located in the Jazan region of southwestern Saudi Arabia. The population of Jazan is relatively homogeneous, with inhabitants habitually sharing the same language, ethnicity and religion [28].

This investigation represents a 24-week (in total) parallel randomized controlled trial (Figure 1). After screening for eligibility and enrolment, participants will then be individually randomized by a computer program (Random Allocation Software) to 12-weeks of: (1). Home-based physical activity or (2). Control group. Primary and secondary outcome variables, as described in detail below, will be assessed at baseline, 12-weeks and at follow-up (24-weeks). In agreement with previous trials of type-2 diabetes management, the primary outcome measure will be the between-group difference in HbA1c [29,30]. Secondary outcome measures will be between-group differences in anthropometric, blood pressure, resting heart rate, blood biomarkers, physical fitness, and patient-reported outcome indices.

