### 2.4. Sample Size

Power calculations were performed for the primary outcome variable i.e., the between groups difference in HbA1c. An a priori power analysis was undertaken with a significance level of 5% and 80% power, based on previous HbA1c values at baseline and at 12-weeks (of a longer duration trial) following a physical activity intervention in patients with type-2 diabetes [29]. Taking into account an expected loss to follow-up rate of 20%, this revealed that 31 participants would be required in each trial arm with a total N of 62.

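### The primary outcome, HbA1c, has no primary time point: it is tested at 12 and at 24 weeks, each at 0.05, although the sample size rests on one comparison using 12-week values

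*Protocol article*

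**What the plan says.** **Definition of the primary outcome.** The Abstract has "The primary study outcome is the between-group difference in blood HbA1c levels relative to controls", and section 2.1 has "the primary outcome measure will be the between-group difference in HbA1c". Neither attaches a visit. Sections 1.1 (Aims), 1.2 (Hypotheses), 2.4 (Sample Size) and 2.12 (Blood Biomarkers) do not supply one either.

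**Visits.** Section 2.1 says that primary and secondary outcomes "will be assessed at baseline, 12-weeks and at follow-up (24-weeks"). The programme lasts 12 weeks, so the 24-week visit falls 12 weeks after it ends.

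**Sizing.** Section 2.4 sets 5% significance and 80% power. It describes the inputs to the calculation as "based on previous HbA1c values at baseline and at 12-weeks (of a longer duration trial"). With 20% loss to follow-up this gives 31 per arm, 62 in total.

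**Analysis.** Section 2.16, for all outcome measures: "differences between the two groups will be examined using linear mixed models (at both 12-weeks and follow-up"), adjusted for baseline. It adds that "changes from baseline to follow-up in HbA1c will be used to create a binary variable" (improved or not), compared between arms by a chi-square test with a Monte Carlo p-value. One threshold, p ≤ 0.05, covers all analyses. No test is ranked above another.

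**The concern.** The two visits answer different questions. Week 12 asks whether the programme lowers HbA1c; week 24 asks whether any benefit lasts after the programme has stopped. They can easily disagree, and the article does not say which one settles the hypothesis in section 1.2. A reader could not tell a trial that met its primary endpoint from one that met it at the more favourable of two visits.

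The signals in the text also point both ways. The sizing uses 12 weeks, while the improvement variable uses the change from baseline to 24 weeks. The trial was sized for one HbA1c comparison at 5%. If either visit may carry the claim, the claim as a whole is not controlled at that level.

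**Working it through.** **Inputs from the article:** significance level 5%, power 80%, loss to follow-up 20%, 31 per arm (section 2.4); two baseline-adjusted HbA1c tests, one improvement test, threshold 0.05 (section 2.16).

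**Assumptions, because the article does not give them:** two-sided tests; correlation of HbA1c between baseline and each later visit 0.5–0.8, and between 12 and 24 weeks 0.3–0.9.

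**Step 1. The stated sample size.** It cannot be reproduced forward, because no HbA1c difference or SD is given. Working back: 31 × 0.8 = 24.8, so about 25 completers per arm (25/0.8 = 31.25, which is 31 when rounded to the nearest whole number). The implied standardised difference is (1.960 + 0.842) × √(2/25) = 0.79 by the normal approximation, or 0.81 with the t distribution. This fits a single test at 5%.

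**Step 2. Two visits at 0.05.**
- Upper bound: 0.05 + 0.05 = 10%.
- Independent tests: 1 − 0.95² = 9.75%.
- Correlated test statistics (bivariate normal, at least one |Z| > 1.96): 9.1% at 0.5, 8.4% at 0.7, 7.8% at 0.8.

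These count false positives in either direction. If only false claims of benefit count, one test gives 2.5% and two independent tests give 1 − 0.975² = 4.9%, so the relative inflation is about the same.

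**Step 3. Simulation under no effect.** 25 completers per arm, 20,000 trials per setting, baseline-adjusted comparison at each visit, and the improvement test at 24 weeks. The conditional p-value is the quantity that a Monte Carlo chi-square p-value estimates.

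| Correlation baseline–later | Correlation 12–24 weeks | Either visit | Any of three, conditional p | Any of three, asymptotic p |
|---|---|---|---|---|
| 0.5 | 0.3 | 9.8% | 11.6% | 14.0% |
| 0.5 | 0.5 | 9.1% | 11.1% | 13.4% |
| 0.5 | 0.7 | 8.7% | 10.5% | 13.0% |
| 0.7 | 0.7 | 9.4% | 11.1% | 13.6% |
| 0.7 | 0.8 | 8.8% | 10.4% | 12.8% |
| 0.7 | 0.9 | 7.9% | 9.6% | 11.9% |
| 0.8 | 0.9 | 8.5% | 10.0% | 12.3% |

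Each visit's test taken alone rejected in 4.8–5.2% of trials. The improvement test alone rejected in 3.1–3.4% with the conditional p-value and 6.4–6.6% with the asymptotic one.

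**Step 4. The alternative of keeping both visits as co-equal.** With 0.025 each, the critical value is 2.241, and power at the implied difference is Φ(2.802 − 2.241) = 71%. Restoring 80% needs 2 × (2.241 + 0.842)² / 0.792² = 30.3, so 31 completers per arm; 31/0.8 = 38.75, so 39 randomised per arm and N = 78.

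**The case against.** **The intended visit can be inferred.** Section 2.4 takes 12-week values out of a longer trial, section 1.1 speaks of a 12-week programme, and the article calls 24 weeks the follow-up. Twelve weeks is the natural reading. That stands, and it makes the repair easy, but it remains an inference: no sentence designates that visit, and section 2.16 treats the two alike.

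**An article may leave this to a full analysis plan.** That holds for a detailed multiplicity procedure. The visit, however, is part of what the primary outcome is. Section 2.16 is also not silent: it fixes testing at both visits at one threshold.

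**Three stronger readings are tempting and are not supported.**
- *That the 5% level simply fails.* It does not fail for any single HbA1c test at a visit. The inflation arises only if the claim may rest on either visit, and no passage states such a success rule.
- *That three results compete as primary, with error near 14%.* The improvement comparison is a difference in proportions, comes last in section 2.16 and is never called primary. The 12–14% range belongs to an asymptotic chi-square p-value, whereas the article specifies Monte Carlo p-values, for which the figure is about 10–12%.
- *That the registration has the same gap.* The record is not among the documents and may already give a time frame.

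**Conclusion.** The point holds in a limited form. The article leaves the primary time point open and tests the primary outcome at two visits at the full 5% each. A primary claim allowed from either visit would carry about 8–10% error; adding the improvement test brings this to about 10–12%. The exact figures depend on assumed correlations and on about 25 completers per arm, but every setting examined is above 5%. The missing designation depends on none of these assumptions. It should be corrected before results are seen, because choosing a visit afterwards cannot restore the error rate.

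**What to change.** Name the baseline-adjusted group difference in HbA1c at 12 weeks as the single primary endpoint, tested at 0.05. This is the end of the programme and the visit whose data underlie the sizing ("based on previous HbA1c values at baseline and at 12-weeks"). Make the 24-week difference a secondary measure of persistence and label the improved/not-improved comparison as supportive. Use the same wording in the Abstract and in sections 1.1, 2.1, 2.4 and 2.16, and check that it agrees with the registration. Section 2.17 already provides for ethics re-review and a registry amendment if one is needed.

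Cost: wording only. N stays at 62 and the significance level at 5%. What is given up is the option of resting the primary claim on the 24-week result.

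### The improve/did not improve test on 24-week HbA1c is an unadjusted chi-square with much less power than the baseline-adjusted continuous analysis already planned, so it should be explicitly supportive and baseline-adjusted, or dropped

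*Protocol article*

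**What the plan says.** The primary outcome is continuous. Section 2.1 states that "the primary outcome measure will be the between-group difference in HbA1c", and outcomes "will be assessed at baseline, 12-weeks and at follow-up (24-weeks" weeks being the label for the last visit. The Abstract gives the length of the programme: "This 24-week investigation will involve 12-weeks of physical activity in the physical activity group".

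Section 2.16 contains two analyses of HbA1c:

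- **Continuous.** For all outcome measures, "differences between the two groups will be examined using linear mixed models (at both 12-weeks and follow-up", and these models are "adjusted for baseline values modelled as a continuous fixed covariate". A mean difference with its 95% confidence interval is to be reported.
- **Binary.** At the end of the section, "changes from baseline to follow-up in HbA1c will be used to create a binary variable i.e., improve/did not improve". Then "Pearson chi-square tests of independence will be used to undertake bivariate cross-tabulation comparisons between the two trial groups", and "Chi-square probability values will be calculated using Monte Carlo simulation". No covariate enters this comparison, and no effect estimate or interval is described for it.

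One significance level, p ≤ 0.05, applies to all analyses. The section does not say how the binary result ranks against the continuous one.

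**The concern.** The binary test concerns the same variable as the primary outcome. It reduces each participant's change to a yes or no and drops the baseline adjustment used in the model described just before it. Both steps discard information, and the trial is small: 62 randomised, with 20% loss expected.

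Interpretation is what is at stake. Readers find a responder result easy to quote, and here it is a stand-alone test at the same p ≤ 0.05. If the programme works as well as the sample size presumes, the two analyses of HbA1c could easily disagree, with the continuous contrast significant and the responder test not. The plan does not say which then carries the conclusion, so the weaker test could be read as evidence of no effect.

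**Working it through.** **Inputs from the protocol article.** Section 2.4 gives 5% significance, 80% power, 20% loss and 31 per arm. Section 2.16 gives the two analyses.

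**Assumptions.** Two-sided testing (not stated), normally distributed change with equal SD in both arms, no mean change in controls, and any fall counted as improvement.

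**Step 1: the plan's own figure.** The 62 cannot be reproduced, because Section 2.4 gives no effect size or SD. It can be solved backwards. Evaluable per arm: 31 × 0.8 = 24.8, about 25. With 25 per arm, 80% power on a two-sided t-test needs a standardised difference of 0.81 (0.79 by the normal approximation). I use d = 0.8 in units of the SD of change.

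**Step 2: proportions improving.** P(improve) = Φ(mean fall / SD of change).

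- Control: Φ(0) = 50%.
- Intervention: Φ(0.8) = 79%.

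**Step 3: power of the responder test, 25 per arm.**

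- Normal approximation: pooled proportion 0.644; null SE = √(2 × 0.644 × 0.356 / 25) = 0.135; alternative SE = √((0.25 + 0.167) / 25) = 0.129. Power = Φ((0.288 − 1.96 × 0.135) / 0.129), about 57%.
- Exact enumeration of the Pearson test: 60%. This is slightly flattering, because at a 50% rate in both arms the test rejects 6.5% of the time, not 5%.
- Exact enumeration with fixed margins, which a Monte Carlo p-value is assumed to approximate: 47% (it rejects 3.3% under the null).

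By the normal approximation, about 43 evaluable per arm would be needed for 80% power, against 25.

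**Step 4: power on the continuous scale, 25 per arm.**

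- Change, unadjusted: noncentrality 0.8 × √(25/2) = 2.83 on 48 df, power 79% (81% by the normal approximation).
- Adjusted for baseline: with baseline-to-follow-up correlation r, the residual SD is √((1 + r)/2) times the SD of change. For r = 0.5 the factor is 0.866 and d becomes 0.8 / 0.866 = 0.924, power 89%. For r = 0.8 the factor is 0.949 and d becomes 0.843, power 83%. The correlation is an assumed range.

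**Step 5: other effect sizes.** Section 2.4 rests on 12-week values, so 0.8 SD may not apply at 24 weeks.

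| Effect (SD of change) | Improve, control v intervention | Pearson | Fixed margins | Continuous, adjusted (r = 0.8 to 0.5) |
|---|---|---|---|---|
| 0.8 | 50% v 79% | 60% | 47% | 83% to 89% |
| 0.6 | 50% v 73% | 41% | 29% | 59% to 67% |
| 0.4 | 50% v 66% | 23% | 15% | 31% to 36% |

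With a control mean change of ±0.25 SD and d = 0.8, Pearson power is 55% to 64% and fixed-margin power 40% to 53%. The responder test is weaker in every case.

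**Step 6: what adjustment of the binary comparison recovers.** In simulation at about 0.8 SD, a baseline-adjusted binary model has 61% to 67% power. That is somewhat better than the chi-square but well short of the continuous analysis.

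**The case against.** The strongest reply is that nothing important depends on this test. The primary outcome is the continuous difference, the sample size was set for it, and Section 2.16 analyses it with baseline adjustment at both visits. The responder table comes last, and a supplementary analysis need not have 80% power. An unadjusted comparison of randomised arms is also valid. All of this stands, and it limits the point to how the responder result is ranked, analysed and read. It does not remove it, because Section 2.16 fixes the visit, the variable and the test, and applies the common significance level without saying that the result is supportive.

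Several stronger readings are tempting, but the documents do not support them:

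- **The test mostly measures noise.** The article gives no HbA1c effect, SD or assay error. At the effect implied by the sample size the arms separate 50% v 79%, which is real signal.
- **Any fall, however small, counts.** This is the natural reading of improve/did not improve, and I use it for the calculation, but the text does not say it. A cut-off may sit in a fuller plan that is not shown. A different cut-off would not remove the loss: for a small shift in a normal variable, splitting is at best 2/π = 64% efficient, and that is reached with a split at the centre.
- **It contradicts intention to treat.** Section 2.16 includes all randomised participants only as far as the collected data allow, and it does not say how a missing 24-week value is classed.
- **A high control rate would look like benefit.** Chance improvers occur in both arms. They do not create a difference in a between-arm test.
- **Testing at 24 weeks is an error.** The visit falls 24 − 12 = 12 weeks after the programme ends, but it is a planned follow-up. Asking whether improvement lasts is legitimate.

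**Conclusion.** The point holds as one of efficiency and interpretation. Under the stated assumptions at 0.8 SD, the planned responder test has about 60% power, or about 47% if the Monte Carlo p-value conditions on the margins. The baseline-adjusted continuous analysis in the same section has 83% to 89%. So even if the programme works as the sample size presumes, the responder test would miss the effect in about 40% of trials, or about 53% with fixed margins. A non-significant result would say little.

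The absolute figures depend on an effect solved backwards from 12-week sizing, two-sided testing, normal changes, a zero cut-off and an assumed correlation of 0.5 to 0.8. The ordering does not change across the effect sizes and control changes tried. The primary analysis is not damaged. This is a correction worth making, not a threat to the trial's main inference.

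**What to change.** In Section 2.16:

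1. State that the responder comparison is supportive, and that the conclusion on HbA1c is drawn from the baseline-adjusted continuous contrast.
2. Replace the unadjusted chi-square with a binary model that includes baseline HbA1c as a covariate, and report the adjusted risk difference with its 95% CI. Alternatively, drop the test and show the distribution of HbA1c change by arm.

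The first change matters most, because adjusting the binary model recovers only part of the lost power. An interval also shows directly how wide the uncertainty is when the result is not significant.

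The cost is small: a change of wording before analysis, slightly more analysis work, and one fewer stand-alone significance test to report. Baseline HbA1c is already measured, so data collection and recruitment do not change.

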### 2.17. Ethics and Dissemination

This study has been granted ethical approval by the University of Jazan, Health Research Ethics Committee (REF: 2177) and formally registered as a trial (NCT04937296). Any required alterations to the experimental protocol will be sent for re-review/approval by the research ethics committee and amended at the trial registry. Participants who express a desire to view a summary of the trial findings will be provided with such information when the data have been analysed. Dissemination of the study findings from this investigation will be through publication in a leading peer-reviewed journal and presentation at both national and international scientific conferences.

